#### Secondary analyses

The mean and standard error for each of the following variables will be determined for each study group. The change from baseline to end of study will be compared between groups using repeated measures ANOVA and using nonparametric tests if necessary, for the following variables: body weight, waist circumference, BMI, blood pressure, serum levels of 25(OH)D, blood glucose, HbA1c, insulin, IGF-1, lipids, CRP, estradiol, testosterone, SHBG, specific microRNAs, dietary glycemic index, number of steps per day and quality of life. We will also test treatment differences in medication use and medication side effects. Chi-square test will be used to compare categorical variables and Student t-test or Wilcoxon test for continuous variables. The association between each variable and prognosis will be analyzed using Cox proportional hazard model and logistic regression. Finally, we will assess whether these secondary analyses are different at year 1 compared to end of study. All statistical analyses will be conducted with SPSS statistical software version 23.0 (SPSS Inc., Chicago IL, USA).

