### Recruitment and randomization

Eligible participants are recruited in five oncologic centres in Italy (four in Southern Italy and one in Northern Italy). Details of the recruiting centres can be found in Table 3. Eligible participants are contacted either by phone or during one of their follow-up visits and offered to hear more about the study during an information session (either group session or a one-to-one session to accommodate all needs). Eligible participants are explained the study details and are given an informed consent document to take home which they bring back at the baseline visit. At the baseline visit, after obtaining written consent the participant is sent for a blood test and other measurements, is randomized to one of the two arms of the study, receives the advice on the program according to her randomization arm and is given the next appointment slip. Participants are contacted by phone monthly for the first three months and once between visits afterwards. Study visits are scheduled every 3 months until end of study (33 months).

Randomization is done electronically in real time for all recruiting centres and is stratified by stage (I/IIA vs. IIB/IIIA) and age (<50 yrs or ≥50 yrs) at diagnosis and is based on a permuted block design with block size of 4. Stratification by stage and age is done because we expect these variables to affect the outcomes. To prevent any possible study bias the randomization sequence will be done off-site by a third party statistician (Contract Research Organization, Naples, Italy) who will not have contacts with the study participants. The PI is blinded to the randomization of the study participants but not the staff involved in the clinic visits.

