### Outcome measures

Figure 1 depicts the timing and frequency of all study measures. Blood analyses, blood pressure, anthropometric measurements and 7-day food records are taken at baseline and every 3 months afterwards until end of study (up to 33 months). Complete blood analyses are done at baseline, 1 year and end of study while blood analysis pertinent to the treatment are done every three months (Table 5). The primary outcome is the percentage of patients alive at end of study without BC recurrence (disease in the same or opposite breast or any metastasis). The primary outcome is assessed at each collaborating centre by the collaborating oncologist and confirmed by hospital pathological results which are communicated to the coordinating centre. Secondary end points include glycemic control including blood glucose and glycated hemoglobin (HbA1c), cardiometabolic variables including body weight, waist circumference, body mass index (BMI), blood pressure, C-reactive protein (CRP) and blood lipids, hormonal measures including insulin, insulin-like growth factor-1 (IGF-1), estradiol, testosterone and sex hormone binding globulin (SHBG), and epigenetic markers (microRNA). Program adherence and any difficulty noticed, medications and medication changes, as well as any unusual or adverse events, including illness or stressful issues, that occurred since the last clinic visit are recorded in detail.

**Table 5 Tab5:** Blood analyses performed during the study

Parameters	Baseline, 12 mo and study end	Every 3 months
25(OH)D	x	x
Calcium	x	x
Glucose	x	x
HbA1c	x	x
Insulin	x	
Triglycerides	x	
Total Cholesterol	x	
LDL-C	x	
HDL-C	x	
AST/ALT	x	
CRP	x	
Estradiol	x	
Testosterone	x	
SHBG	x	
IGF-1	x	
microRNA	x	
For future analyses	x	x

*AST/ALT*: aspartate transaminase/alanine transaminase, *CRP*: C-reactive protein, *HbA1c*: hemoglobin A1c, *HDL-C*: high density lipoprotein cholesterol, *IGF-1*: insulin-like growth factor-1, *LDL-C*: low density lipoprotein cholesterol, *SHBG*: sex hormone binding globulin, *25(OH)D*: 25-hydroxyvitamin D.

Blood samples and all information regarding the patient are sent to the coordinating centre where blood samples are centrally analyzed and information entered electronically and statistically analyzed for the interim and end of study reports.

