### Statistical analyses

All randomized patients will be analysed considering the “intention-to-treat” principle (ITT analysis). Results will be expressed as percentages or means ± SEM or 95% confidence intervals (CI).

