#### Primary analyses

The primary analyses will assess the between-treatment difference in BC recurrence measured as disease-free survival (DFS), calculated as the percentage of patients alive without recurrence of disease at study end (up to 33 months from randomization). BC recurrence is defined as the relapse of the disease or metastasis either in the same breast (including new positive lymph nodes), or the opposite breast or in distant organs. The duration of DFS in patients lost at follow-up will be censured at the date of the last day the patient was considered free of disease. Between-treatment differences in DFS will be analyzed by *log-rank* test. Kaplan-Meier curves will be provided to estimate median DFS and 95% CI. To address the impact of potential imbalance in prognostic factors we will repeat the primary analysis using the *log-rank* test stratified by stage, age, family history of BC, time since diagnosis, molecular subtype, medication use, smoking, baseline waist circumference and dietary variables (baseline GI, dietary fiber, saturated fat, vegetables/fruit, meat, sweets/desserts). Missing data for covariates will be handled by using the missing indicator method.

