#### Sensitivity analyses

To assess the robustness of our ITT primary analysis with possible missing data we will repeat the primary analysis using completers data only as well as per-protocol data only, using multiple imputation method to generate missing data in the stratification step. To assess the impact of participant-level factors on the primary outcome we will examine DFS separately in those who, at study end, have reached normo-glycemia (<110 mg/dl) and normal levels of HbA1c <6.0% versus those who have higher levels, in those who reached circulating 25(OH)D ≥60 ng/ml versus those who reached ≤30 ng/ml, in those who have lower versus those who have higher insulin levels (median will be used as cut-offs), in those who have good overall compliance on the three treatment components that is in the highest quantile of: low GI + number of daily steps + levels of 25(OH)D, versus those who have lower compliance. For these analyses study end is defined as the mean of the last three visits.

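### Secondary outcomes are compared as unadjusted change by repeated measures ANOVA, which in its classical form excludes women missing any entered visit and is less precise than a baseline-adjusted mixed model

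*Protocol article*

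**What the plan says.** The section Secondary analyses of the protocol article fixes the method for about 18 variables, from body weight to quality of life: "The change from baseline to end of study will be compared between groups using repeated measures ANOVA and using nonparametric tests if necessary". It names no baseline covariate. It then adds: "Finally, we will assess whether these secondary analyses are different at year 1 compared to end of study". SPSS 23.0 is the software, but no procedure within it is named.

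The section Statistical analyses opens with the population: "All randomized patients will be analysed considering the" intention-to-treat principle.

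Two missing-data rules are given, both within the DFS analysis:
- Primary analyses: "Missing data for covariates will be handled by using the missing indicator method".
- Sensitivity analyses: "using multiple imputation method to generate missing data in the stratification step".

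On timing, Outcome measures says that blood analyses, blood pressure, anthropometry and food records "are taken at baseline and every 3 months afterwards until end of study (up to 33 months", and then qualifies this for the blood tests: "Complete blood analyses are done at baseline, 1 year and end of study while blood analysis pertinent to the treatment are done every three months". In Table 5, 25(OH)D, glucose and HbA1c are quarterly. Insulin, lipids, CRP, estradiol, testosterone, SHBG, IGF-1 and microRNA are measured only at baseline, 12 months and study end.

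**The concern.** Classical repeated measures ANOVA needs a complete row for each patient. A woman without one of the entered measurements drops out of the comparison, although the section is headed by a commitment to analyse everyone randomized. Neither missing-data rule helps, because neither concerns a missing secondary outcome value. Missing values are foreseeable: the article provides for patients lost to follow-up (Primary analyses) and allows withdrawal at any time (Ethical considerations).

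There is also a cost in precision. Baseline is measured for every outcome, yet an unadjusted change score does not use it as a covariate.

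At stake are the comparisons behind the stated secondary objectives on diabetes markers, cardiometabolic health and quality of life.

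**Working it through.** **No figure to reproduce.** The article gives no power, precision, dropout rate or baseline correlation for the secondary outcomes. From the documents I take 253 women per arm (Sample size) and visits every 3 months to month 33, so 33/3 = 11 post-baseline visits (Recruitment and randomization). Missingness m and correlation r are assumptions, shown as ranges.

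**1. Women kept by a complete-row analysis.** Baseline measurements are taken at the randomization visit, so only post-baseline visits are treated as missable. With k such visits entered and independent missingness m per visit, the share with complete rows is (1 − m)^k. The number per arm out of 253 is in brackets.

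| m (assumed) | end only, k = 1 | month 12 and end, k = 2 | all visits, k = 11 |
|---|---|---|---|
| 2% | 98% (248) | 96% (243) | 80% (203) |
| 5% | 95% (240) | 90% (228) | 57% (144) |
| 10% | 90% (228) | 81% (205) | 31% (79) |

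At 5% the losses are therefore about 5%, 10% and 43%. For the markers measured three times, k cannot exceed 2.

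**2. What each reading tests.** With baseline and end only, the arm-by-time test is the t-test on change scores, and the 10 intermediate visits of the quarterly measures go unused. With all visits, the arm-by-time test asks whether the profiles differ anywhere over time, which is not the baseline-to-end contrast that the article names.

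**3. Precision of the change score.** Take equal variances s² at baseline and end. An unadjusted change has variance 2(1 − r)s². Adjusted for baseline, the variance is (1 − r²)s². The ratio is (1 − r²)/[2(1 − r)] = (1 + r)/2, below 1 for any r < 1.

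| r (assumed) | change | adjusted | ratio | adjusted n per arm equivalent to 253 on change |
|---|---|---|---|---|
| 0.3 | 1.40 | 0.91 | 0.65 | 164 |
| 0.5 | 1.00 | 0.75 | 0.75 | 190 |
| 0.7 | 0.60 | 0.51 | 0.85 | 215 |
| 0.9 | 0.20 | 0.19 | 0.95 | 240 |

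For an assumed difference of 0.2 SD and 253 per arm with complete data, power is 61% on change and 74% with adjustment at r = 0.5, and 83% against 88% at r = 0.7.

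**4. Simulation check.** 2,000 runs, 253 per arm, 12 visits, assumed correlation 0.6, true end difference −0.25 SD, 3% intermittent missingness, and dropout that in the HIT arm depends on the preceding value.
- 63% of women had complete rows over all visits; 86% had an end value.
- The standard error of the change-score difference was 0.077 with full data, 0.084 with an end value required, and 0.098 with complete rows required.
- With full data, baseline adjustment gave 0.0695 against 0.0770, a variance ratio of 0.0695²/0.0770² = 0.81, close to (1 + 0.6)/2 = 0.80.
- Among women with an end value, the change score averaged −0.247, close to the truth, but end-visit ANCOVA averaged −0.273. Adding a baseline covariate to a completers-only analysis is therefore not a sufficient repair. The mixed model was not part of this simulation.

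**The case against.** The strongest reply is that the harm depends on an implementation that the article does not specify. It names a baseline-to-end change and a year 1 comparison, and never says that all quarterly visits enter. If only baseline, month 12 and end are used, an assumed 5% per visit costs 10% of women, not 43%. Many listed markers are measured only three times in any case, and misses that cluster in the same women would leave more complete rows than the independence formula gives. All of this stands.

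A reader might also infer the following, and the documents do not support any of it:
- *Intention-to-treat is broken outright.* SPSS can fit a likelihood-based mixed model, and the article neither names nor excludes one. The conflict arises with the classical form of the named method.
- *The comparison would be among recurrence-free completers.* Nothing says that visits stop after recurrence.
- *Selection will differ by arm because HIT asks more.* This is possible, but Study design says that both arms get the same follow-up visits and blood tests, to help compliance.
- *The two losses add up.* The (1 + r)/2 ratio belongs to a baseline-to-end change score; the 43% belongs to a full-schedule ANOVA.

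It is also true that an unadjusted change score is unbiased in a randomized trial with complete data. The criterion for switching to nonparametric tests, and any log-transformation, are details commonly left to an analysis plan, and I do not press them.

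What the reply does not remove is that the article fixes the method, omits a baseline covariate, and gives no missing-data rule that reaches these outcomes.

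**Conclusion.** The point holds as an improvement to make to the secondary analyses. The named method, in its classical form, excludes women who lack an entered visit and so fits poorly with the intention-to-treat statement. At an assumed independent 5% missing per visit the loss runs from 5% to 43%, according to which visits enter. It would be wrong to say that every woman with a missed visit is dropped, since that is true only if the whole schedule enters an ANOVA that requires complete rows.

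The precision loss of an unadjusted baseline-to-end change does not depend on missing data: for assumed r from 0.9 down to 0.3, adjustment would lower the variance by 5% to 35%. Missingness rates, their independence and r are all assumptions. The primary log-rank analysis of DFS is untouched.

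**What to change.** In Secondary analyses, replace the ANOVA on change with a likelihood-based mixed model for repeated measures (MIXED in the planned SPSS), using all available post-baseline values:
- Fixed terms: baseline value, randomization strata (stage, age), visit, arm and arm-by-visit.
- Main estimate: the between-arm contrast at month 33. Month 12 comes from the same model and serves the year 1 comparison.
- Visits: all scheduled post-baseline visits for the quarterly measures; month 12 and study end for the markers that Table 5 schedules only then.
- Missing data: state the missing-at-random assumption and add a sensitivity analysis that departs from it.

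The cost is a little more programming and an explicit reliance on missing at random. No new data, visits or software are needed. A woman with no post-baseline value still contributes nothing, so the model comes closer to analysing all randomized patients without literally achieving it.

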### Participants

Women who had undergone surgery for primary histologically confirmed BC, stages I-III (see Tables 1 and 2 for details), within the previous 12 months in cancer centres in Italy, who are between the ages 30–74 years and have no contraindications to participate in this study will be eligible to participate. Eligibility is confirmed by central reviewing of medical records and pathology reports. The inclusion and exclusion criteria are summarized in Table 1. To participate in the study each potential participant is required to read and sign the study information/consent form at baseline.

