
Physical activity after BC diagnosis has also been shown to reduce the risk of BC mortality by 40-50% particularly when it is of moderate intensity such as 30 minutes of brisk walking per day [32–35]. This effect may be modulated partly by reduced insulin, insulin-like growth factors and estrogen levels [36, 79, 80] which are associated with BC recurrence and death [81, 82]. Furthermore, physical activity can improve insulin sensitivity, reduce blood triglycerides, blood pressure and body fat [83–85]. The lifestyle changes proposed in this study (lower dietary GI, enhanced Mediterranean diet, physical activity) may also induce weight loss which in turn may improve insulin sensitivity, IGF profile and reduce aromatase activity in adipose tissue with consequent reduction in estrogen levels [86], particularly relevant in postmenopausal women [87]. Although weight loss is not a goal of the DEDiCa study, participants will be allowed to lose weight in situations of overwheight or obesity should they wish to. The secondary statistical analyses will take into consideration this aspect.

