
DEDiCa study includes treatment components such as low GI, traditional Mediterranean foods, high dietary fiber and physical activity which have been shown to reduce risk factors for type two diabetes and CVD including HbA1c, blood glucose and lipids, and inflammatory factors [15, 20, 22, 23, 25–28, 30, 60, 98–100].

This study will contribute to understanding the efficacy of lifestyle changes in a Mediterranean population of BC survivors with respect to several novel aspects: testing a lifestyle modification (diet and exercise) within normal vitamin D levels on disease-free survival; investigate lifestyle changes in relation to BC staging, molecular subtypes, menopausal status, body weight, CVD risk factors and events, diabetes control, new diabetes cases, quality of life, response to medication. It will also allow to understand breast carcinogenesis and the role of microRNA in BC and whether they are modulated by dietary and other lifestyle aspects. It will allow to investigate best time of treatment adherence since women will be enrolled within 12 months of surgery, some will have just started their cancer therapy and some will have ended.

Given the supporting evidence of important health effects and safety of the components of DEDiCa intervention we believe it is feasible and urgent to test this program in BC patients.

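### Estradiol change is compared between arms in one pooled analysis, with no log scale and no menopausal or age-stratum term; this costs precision and interpretability for one secondary endpoint.

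*Protocol article*

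**What the plan says.** The Secondary analyses section treats estradiol like every other secondary variable. "The mean and standard error for each of the following variables will be determined for each study group", and then "The change from baseline to end of study will be compared between groups using repeated measures ANOVA" "and using nonparametric tests if necessary". The variable list includes "lipids, CRP, estradiol, testosterone, SHBG, specific microRNAs". No condition triggers the nonparametric route, no transformation is named, and no menopausal or age term appears.

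Four other places bear on this:

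- **Participants:** women are eligible "who are between the ages 30–74 years".
- **Recruitment and randomization:** allocation is stratified by age at diagnosis, below 50 against 50 and over, because age is expected to influence the outcomes.
- **Outcome measures, Table 5:** estradiol is measured at baseline, 12 months and study end.
- **Discussion:** the fall in estrogen through adipose aromatase after weight loss is called "particularly relevant in postmenopausal women". The study is also to "investigate lifestyle changes in relation to BC staging, molecular subtypes, menopausal status", among other factors, without linking this to estradiol or to any model.

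**The concern.** The age range brings together premenopausal and postmenopausal women, whose estradiol levels can be expected to differ in scale. When change is averaged in absolute units, the group with the higher and more variable level dominates the standard error, and the mean difference is weighted towards whatever happens in that group. The result is a noisy estimate that describes neither group well.

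Estrogen is one of the mechanisms by which the programme is meant to work, and estradiol is a listed secondary endpoint. A non-significant pooled result could be read as evidence against that mechanism when the analysis had little chance of detecting it. A later split by menopausal status would then be post hoc.

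**Working it through.** The article gives no expected effect, SD or premenopausal share for estradiol, so there is no stated figure to reproduce. Its 506 women (253 per arm) and two-sided alpha of 0.05 are used below; everything else is an assumption.

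**1. Closed form on the raw scale.** Let f be the premenopausal share, k the ratio of premenopausal to postmenopausal SD of change, and 0.3 postmenopausal SD the true effect.

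- Pooled SD = √[(1−f) + f·k²]
- Power = Φ[effect / (SD·√(2/253)) − 1.96], with √(2/253) = 0.0889

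Take f = 0.3, k = 3 and no premenopausal effect. The SD is √(0.7 + 2.7) = 1.844 and the mean effect is 0.7 × 0.3 = 0.21. Then z = 0.21/(1.844 × 0.0889) = 1.28 and power is Φ(−0.68) = 25%. In postmenopausal women only, n = 177 per arm, z = 0.3/√(2/177) = 2.82 and power is 81%.

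| k (f = 0.3) | Pooled, postmenopausal effect only | Pooled, equal absolute effect in both |
|---|---|---|
| 1 | 66% | 92% |
| 3 | 25% | 45% |
| 5 | 13% | 22% |
| 10 | 6% | 9% |

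An inverse-variance stratified test gives 79-82% for k of 3 or more in either column. At k = 1 it equals the pooled test, so the loss comes from unequal variances.

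**2. Proportional effect, simulated.** Estradiol is taken as lognormal with a baseline log SD of 0.6. The premenopausal geometric mean is 2 to 12 times the postmenopausal one, and 20-40% of women are premenopausal. The SD of log change is 0.8 (premenopausal) and 0.5 (postmenopausal), and the programme lowers estradiol by 15%. The pooled test is a t-test on raw change.

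| Analysis | Only postmenopausal women respond | Both respond |
|---|---|---|
| Pooled raw change | 5-21% | 16-43% |
| Pooled rank test (ratio 3 to 12) | 26-66% | 65-83% |

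Over both columns, the stratified log-scale test has 71-93% power. If the two log-change SDs are equal, pooled raw power rises to as much as 80%, the rank test reaches up to 92% when both groups respond, and the stratified log-scale test has 58-97%. Simulation error and the assumed baseline spread move these ranges by a few percentage points.

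**3. Which contrast should lead?** On the log scale a 15% fall is ln 0.85 = −0.1625. With f = 0.3, the postmenopausal subset has z = (0.1625/0.5)·√(177/2) = 3.06, or 86% power. For the stratified contrast the weights are 0.7/0.5² = 2.80 and 0.3/0.8² = 0.469, and SE = √[(2/253)/3.269] = 0.0492.

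- Both groups respond: z = 0.1625/0.0492 = 3.30, power 91%.
- Only postmenopausal women respond: estimate 2.80 × 0.1625/3.269 = 0.139, z = 2.83, power 81%.
- Equal log SDs of 0.5: SE = √[(2/253)/4] = 0.0445. Power is 96% if both respond (z = 3.66) and 73% if only postmenopausal women do (z = 0.7 × 0.1625/0.0445 = 2.56).

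The subset is stronger only if premenopausal women do not respond.

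**The case against.** The strongest reply is that this is a condensed article, and that scale, covariates and subgroups for one of about 18 variables belong in a full protocol or analysis plan. The Discussion already announces an interest in menopausal status. This stands in part: the article does not rule out a covariate or a transformation, and a fuller document may supply them. But the section does state the summary measure, the test and the fallback for estradiol by name. A mean with standard error and an ANOVA on change, with no transformation named, is naturally read as a raw-scale analysis.

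A second reply is that the skewed data assumed here are exactly where the nonparametric route would be used. That stands as mitigation. The rank test does much better than the raw ANOVA, and recovers most of the loss when both groups respond. It still pools the groups, has no stated trigger and gives no effect estimate by menopausal status.

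A third reply is that every input is assumed. That stands. The Discussion mentions estrogen-deprivation therapy and women at different points of their cancer treatment, so the gap between the groups in this population is unknown. The simulation also uses two time points, not the three planned estradiol measurements.

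A reader might go further and infer that the mechanism concerns only postmenopausal women, so that their subset should be the main result. The documents do not support this. The wording is *particularly*, the aromatase pathway depends on weight loss that is not an aim of the study, and the exercise pathway to lower estrogen is given without a menopausal limit.

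**Conclusion.** The point holds as a matter of precision and interpretation for one secondary endpoint. The stated estradiol analysis pools women across menopause without a log scale or a stratifying term, and a better analysis is available on estradiol data already collected and an age stratum already recorded. Randomisation, stratified by age at 50, protects the comparison, so there is no bias, and the primary analysis is untouched.

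The gain over a pooled raw-scale test is consistent in direction across the ranges simulated: about 5-21% or 16-43% power against 71-93%, for a 15% fall with log-change SDs of 0.8 and 0.5. Its size depends on the level ratio, the premenopausal share, the SDs and who responds, none of which the article gives. In the closed-form model the advantage disappears when the two SDs of raw change are equal.

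It would be tempting to say that premenopausal variation swamps the effect, or that the trial would probably report no estradiol effect. Neither can be stated as fact: the first needs a variance ratio that is not given, and the second ignores the rank fallback, which reaches 65-83% under the main assumptions when both groups respond.

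**What to change.** State for estradiol:

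- Analyse log estradiol and report the arm effect as a ratio of geometric means.
- Stratify by menopausal status at entry, or by the randomisation age stratum (below 50, 50 and over) where status is not recorded, and allow separate variances in the strata.
- Report the stratified overall arm contrast as the estradiol result. Alongside it give the arm-by-stratum interaction and both the premenopausal and the postmenopausal contrasts. Do not make the postmenopausal subset the main result.

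The cost is a change of wording and slightly more analysis work. There are two drawbacks: age 50 is only a proxy for menopause, and if premenopausal women do not respond, the stratified overall contrast has somewhat less power than the postmenopausal subset (81% against 86% in the worked case, 73% against 86% with equal log SDs). The separate contrasts make that situation visible.

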**Methods:**

Women (30-74 yr) who had undergone surgery for primary histologically confirmed BC (stages I-III) within the previous 12 months, in cancer centres in Italy, will be randomized to follow, for a maximum of 33 months, either a high intensity treatment (HIT) composed of low GI diet + exercise + vitamin D (60 ng/mL serum concentration) or a lower intensity treatment (LITE) with general advice to follow a healthy diet and exercise pattern + vitamin D to avoid insufficiency. Both interventions are on a background of a Mediterranean diet. Considering a 20% recurrence rate within 3 years for BC cases and a predicted rate of 10% in the HIT group, with power of 80% and two-sided alpha of 0.05, the subject number required will be 506 (*n* = 253 in each arm). Clinic visits will be scheduled every 3 months. Dietary and exercise counselling and vitamin D supplements will be given at each clinic visit when blood samples, anthropometric measures and 7-day food records will be collected.

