### Sample size

Considering a 20% recurrence rate within 3 years in most collaborating centres for BC cases specified in Table 2, and a predicted rate of 10% in the high intensity arm, with power of 80% and two-sided alpha of 0.05, the number of subjects are 506 (*n* = 253 in each arm).

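### Logistic regression is planned beside Cox for prognosis although follow-up is censored, so a marker related to retention but not to recurrence can show a biased odds ratio

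*Protocol article*

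**What the plan says.** The Secondary analyses section lists 18 variables or groups of variables, from body weight and blood markers to dietary glycemic index, daily steps and quality of life. It then says: "The association between each variable and prognosis will be analyzed using Cox proportional hazard model and logistic regression". Prognosis is not given a separate definition, and neither model is named as the leading one.

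The outcome that carries prognosis in this trial is DFS. The Primary analyses section describes it in two ways. It is a proportion, "calculated as the percentage of patients alive without recurrence of disease at study end (up to 33 months from randomization". It is also a time to event: "The duration of DFS in patients lost at follow-up will be censured at the date of the last day" on which the woman was considered disease-free, and "Between-treatment differences in DFS will be analyzed by *log-rank* test", with Kaplan-Meier curves. The abstract describes the intervention as lasting "for a maximum of 33 months".

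Incomplete follow-up is expected. The Sensitivity analyses section plans for missing data. Ethical considerations lets women withdraw at any time and allows the study to be terminated after an interim analysis. No expected loss rate is stated.

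**The concern.** The Cox model uses each woman's time at risk, so a woman lost at month 6 contributes six months and no more. Ordinary logistic regression needs a yes/no status for everyone it includes. A woman lost before study end has no known status, so she is either counted as event-free, which understates risk where loss is high, or removed. Removal overstates risk where loss is high, because women whose recurrence came before they would have been lost stay in while event-free lost women leave. If loss is related to the marker, the odds ratio is biased, in opposite directions under the two codings.

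A relation between marker and retention is plausible here. The Sensitivity analyses section measures compliance by glycemic index, daily steps and 25(OH)D, and all three are among the variables to be related to prognosis. At stake is whether a variable that only tracks staying in the study is reported as prognostic, with a second model, of no stated rank, offering another chance of a positive result.

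**Working it through.** The article states no figure for this analysis, so there is none to reproduce. The check asks what logistic regression returns for a marker with no effect on recurrence.

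**Inputs from the article.** 506 women (Sample size). Recurrence of 20% and 10% within 3 years in the two arms (Sample size), averaged to 15% at 36 months. Follow-up of 33 months.

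**Assumptions.** A binary marker splitting the women 253/253, constant recurrence hazard, a proportion d lost at times spread evenly over 33 months, and loss independent of recurrence within each marker level.

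**Step 1: event risk.** λ = −ln(0.85)/36 = 0.004514 per month.
- Risk by 33 months: F = 1 − exp(−0.004514 × 33) = 0.1384.
- Average risk up to an evenly spread loss time: A = 1 − F/(33λ) = 1 − 0.1384/0.1490 = 0.0709.

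**Step 2: what is observed at loss d.**
- Observed event: p = (1 − d) × 0.1384 + d × 0.0709.
- Followed to 33 months event-free: c = (1 − d) × 0.8616.

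| Loss d | p | c |
|---|---|---|
| 5% | 0.1350 | 0.8185 |
| 15% | 0.1283 | 0.7324 |
| 10% | 0.1317 | 0.7754 |
| 30% | 0.1182 | 0.6031 |

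**Step 3: odds ratios for a marker with true effect of 1.**
- 5% vs 15%, lost coded event-free: (0.1283/0.8717)/(0.1350/0.8650) = 0.94.
- 5% vs 15%, lost dropped: (0.1283/0.7324)/(0.1350/0.8185) = 1.06.
- 10% vs 30%, lost coded event-free: (0.1182/0.8818)/(0.1317/0.8683) = 0.88.
- 10% vs 30%, lost dropped: (0.1182/0.6031)/(0.1317/0.7754) = 1.15.
- Equal loss: 1.00 under either coding.

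Exponential instead of evenly spread loss times give 0.94/1.06 and 0.87/1.14. A 30-point gap (10% vs 40%) gives 0.83/1.27 with evenly spread and 0.81/1.24 with exponential loss times.

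**Step 4: false positives.** For 10% vs 30%, lost coded event-free, the standard error of the log odds ratio is √Σ[1/(253p) + 1/(253(1 − p))] = 0.269. The shift is ln(0.884) = −0.124, or 0.46 standard errors. The two-sided rejection rate is Φ(−1.96 + 0.46) + Φ(−1.96 − 0.46) = about 7.4%. With exponential loss times it is 7.9% (event-free) or 7.7% (dropped). At 5% vs 15% it is about 5.5%, and at 10% vs 40% with exponential loss times about 12%. In 4,000 simulated trials at 10% vs 30%, logistic regression rejected in 7.5% to 7.7% and the Cox score test in 5.0%.

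**Step 5: do the two models agree?** Simulation with a continuous marker, 506 women, 600 trials per row, exponential loss of 15% at the marker mean:

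| Marker effect on recurrence | Marker effect on loss | Cox HR per SD | Logistic OR per SD (event-free / dropped) | Verdicts differ from Cox (event-free / dropped) |
|---|---|---|---|---|
| none | none | 1.00 | 1.00 / 1.00 | 1.2% / 1.2% |
| none | loss hazard × e^0.7 per SD | 1.00 | 0.93 / 1.08 | 5.5% / 7.3% |
| HR 1.3 per SD | none | 1.29 | 1.32 / 1.32 | 3.3% / 3.2% |
| HR 1.3 per SD | loss hazard × e^0.7 per SD | 1.29 | 1.21 / 1.44 | 25.5% / 18.7% |

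Steeper or heavier loss (e^1.0 per SD, or 25% at the mean) raises disagreement for a null marker to about 10% to 14%.

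**The case against.** **Fixed-time reading.** The article also frames the outcome as a percentage at study end, so Cox for time to event and logistic regression for end-of-study status is a coherent plan. This stands as a description of intent, and a 33-month risk is a legitimate quantity. It does not rescue ordinary logistic regression, because status at 33 months is unknown for a woman censored earlier and neither simple coding removes the bias.

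**Detail left to an analysis plan.** Coding of lost women and ranking of models are details an article may leave out, and their absence is not the point. The point is the named method, applied to an outcome the same article censors.

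**Missed visits are not missing outcomes.** Under Outcome measures, recurrence is assessed by the oncologist at each centre and confirmed by pathology, so a woman who stops lifestyle visits may still have a known status. This stands: it could make loss of DFS information, and its relation to markers, smaller than assumed here.

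**Stronger readings.** A reader might infer that any marker linked to drop-out will appear prognostic, or that every marker will get two conflicting results. The documents support neither. Bias needs loss that differs by marker, at rates the article does not give. A null marker at 10% vs 30% loss is still non-significant in about 92% of trials. With unrelated loss, verdicts differ in only about 1% to 3% of trials. Nor does the point reach the primary comparison, which uses the log-rank test.

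**Conclusion.** The point holds in limited form. The article names a method that ignores time at risk beside one that uses it, for an outcome it censors. When retention differs by marker level, the logistic odds ratio is biased, in a direction set by how lost women are coded. Cox stays at 1 for a null marker provided censoring is independent of recurrence given the marker.

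The size is modest: odds ratios of about 0.94 or 1.06 under 5% vs 15% loss and about 0.88 or 1.15 under 10% vs 30%, with false positives of about 5.5% to 8%. Larger effects need a loss gap near 30 points or a steep relation between marker and loss. All of this rests on assumed loss rates, a 15% average 3-year risk and constant hazards. The affected results are secondary associations. The change is worthwhile because it is cheap, not because the trial's main conclusion is at risk.

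**What to change.** In Secondary analyses, make the Cox model the analysis of prognosis and delete the reference to logistic regression. If a 33-month risk is wanted, restrict it to a stated fixed-time outcome, estimate it with a method that handles censoring (inverse-probability-of-censoring weights or Kaplan-Meier pseudo-observations), and report it as supportive to Cox.

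The cost is one phrase of text and no data. The downside is that a simple odds ratio for end-of-study status is no longer reported, or takes slightly more analysis work to obtain.
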